## Conclusions

4

SOS-moral will sort myocardial viability before randomization to avoid the effect of viability of myocardial on cardiac function. Hence, the real benefits of CTO-PCI on cardiac function among these patients without 100% survival viable myocardial will be assessed. Furthermore, the present trial strictly recruits patients with MVD and concurrent CTO. SOS-moral will provide evidence for the value of CTO-PCI among these selected patients. Nevertheless, there remain several potential limitations in this study. First, SAQ may be affected by factors other than recanalization of CTO artery during the study period. Second, patients with high risk such as those with left main artery disease stenosis ≥50% and severe arrhythmia are not included. Patients with left main artery disease are not eligible because the PCI procedure needs to be individualized. Because cardiac function might be affected by the severe arrhythmia, those with severe arrhythmia will be excluded. Therefore, the outcomes are unable to include all patients at high risk. Third, in a limited study period, the study may be not powered to detected MACE differences between the two groups. Therefore, further studies including high-risk patients and with longer follow-up periods are needed in the future.

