**Methods and results::**

Patients will be prospectively recruited who meet the following criteria:

Patients presenting with no necrosis of myocardial tissue in the territory of the CTO will be excluded. Recruited patients will be randomized into 2 groups: those undergoing PCI of only the non-CTO artery (non-CTO PCI group), and those undergoing PCI of the non-CTO artery concurrently with the CTO artery (CTO-PCI group). The primary outcome will be the change in cardiac function evaluated via CMR at a 12-month of follow-up appointment, which will be compared to a baseline measurement. Secondary outcomes include occurrence of major cardiac events, CMR-assessed myocardial viability in the CTO-supplied territory, and quality of life assessed by Seattle angina questionnaire, Patient Health Questionnaire 9 and Generalized Anxiety Disorder Scale-7 after 12-month follow-up.

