The presence of a CTO and not MVD alone has been reported to be independently associated with long-term mortality and impaired left ventricular eject fraction (LVEF).^[16]^ Hence, the effect of CTO-PCI on cardiac function merits investigation. An early study that recruited patients with at least 1 CTO and a LVEF of ≤ 40% found that CTO-PCI decreased left ventricular end-systolic volume and increased LVEF.^[17]^ Another study, with a small sample size, showed that successful CTO-PCI improved regional wall motion.^[18]^ The EXPLORE trial showed that routine CTO-PCI did not result in an overall benefit with respect to LVEF and lower left ventricular end-diastolic volume (LVEDV) within 4 months, when compared with a non-CTO PCI strategy in an unselected cohort of patients with STEMI and concurrent CTO.^[19]^ An extended examination of the EXPLORE trial also did not reveal beneficial effects associated with routine early CTO-PCI on LVEF within a 1-year period.^[20]^

Myocardial viability affects CTO-PCI outcomes. With respect to myocardial viability, the myocardium in the CTO territory can be divided into groups as follows: complete survival, partial survival, and non-viable myocardium. We predict that conflicting conclusions drawn by previous studies can be partially attributed to the failure to consider the status of myocardial tissue or the burden of ischemia.

At present, US and European guidelines provide Class IIa or IIb recommendations for PCI for the treatment of CTO. The recommendation comes despite the fact that the rate of successful CTO-PCI is more than 90% at experienced centers and can be increased by training of operators working within clinical practices, especially those in small centers. These facilities include a large portion of patients presenting with CTO combined with MVD who receive treatment involving exclusively non-CTO PCI or incomplete revascularization. The purpose of the present trial is to compare the effect of CTO-PCI combined with non-CTO PCI versus non-CTO PCI with respect to cardiac function, myocardial viability, and MACE among patients with MVD and necrotic myocardial tissue. Cardiovascular magnetic resonance (CMR) will be used to assess the viability of the myocardium, which facilitates identification of patients who will benefit from complete revascularization procedures.

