### Study design and randomization

2.1

This SOS-moral study is a randomized controlled trial with a multi-center design. The protocol was approved by the ethics committee of Beijing Anzhen Hospital (approval no. 2017059X) and has been registered at ClinicalTrials.gov (identifier: NCT 03372785).

Patients meeting the inclusion criteria will be categorized into two groups at a ratio of 1:1 according to a randomized digital table used to randomly assign patients to the CTO-PCI group (PCI of both the non-CTO artery and a concurrent CTO artery), or the non-CTO PCI group (PCI of only the non-CTO artery). The randomized digital form and interactive voice response mode will be applied to facilitate the randomization procedure. The randomization sequence will be produced and managed by an independent staff member. Before intervention, myocardial viability and cardiac function of patients will be evaluated using CMR. Cardiac function will be assessed using transthoracic echocardiography and CMR. The Seattle angina questionnaire (SAQ), Patient Health Questionnaire 9 and Generalized Anxiety Disorder Scale-7 will be used to evaluate patient QOL. Cardiac function, QQL, and MACE will be observed within 12 months of follow-up. A flow chart outlining the study design is depicted in Figure 1.

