Early studies reported that successful recanalization CTO can both improve LVEF and ventricular wall movement assessed by CMR, and can improve QOL.^[22–25]^ An early meta-analysis found that successful recanalization of a CTO resulted in an overall improvement of 4.44% absolute LVEF points, reduced remodeling, and improved survival (OR: 0.52).^[26]^ However, the EXPLORE trial showed that in acute STEMI patients with concurrent CTO, CTO-PCI did not increase global LVEF or decrease LVEDV assessed by CMR 4-month post-PCI compared to patients receiving treatment in the non-CTO artery. Interestingly, a subgroup analysis of the EXPLORE trial showed that CTO-PCI in patients with a concurrent CTO in the LAD was associated with significantly higher LVEF levels after 4-month post-PCI compared with non-CTO PCI, suggesting that CTO-PCI may potentially benefit high-risk patients.^[19]^ According to Chung,^[27]^ the benefit of CTO-PCI is controversial with respect to cardiac function and survival among the MVD patients with concurrent CTO. This may partly be because myocardial viability affects the alteration of cardiac function produced by CTO-PCI. An in-depth analysis in the EXPLORE CMR study revealed that CTO-PCI was associated with the greater recovery of regional systolic function relative to baseline values 4-month post PCI in dysfunctional myocardial tissue supplied via CTO. The benefit was most evident in dysfunctional but viable segments (transmural extent of infarction <50%).^[28]^ The investigators opined that the benefit was probably attributable to the recovery of stunned myocardial tissue affected by the acute interruption of blood supply, as well as by the prevention of arrhythmia. Taken together, the data suggest that varying levels of myocardial viability in patients included in previous studies may be associated with reported variations in cardiac functioning observed after successful CTO-PCI treatments. Therefore, myocardial viability should be considered.

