Previously, 128 patients were observed using CMR, and among the myocardial regions that corresponded to 149 CTO lesions, only 11.5% presented as transmural myocardial infarction. In fact, 58.6% of the myocardial segments showed no delayed enhancement.^[29]^ Differences in myocardial viability may contribute to the variable prognosis of CTO-PCI. A previous study including 32 CTO patients presenting with significant inducible perfusion deficits found that recanalization was associated with decreased ischemic burden, improved QOL, and reversed remodeling.^[23]^ The effect of CTO-PCI on cardiac function among patients with necrotic myocardial tissue in the territory supplied by the CTO combined with MVD requires further investigation. The present SOS-moral study excludes those patients with complete myocardial survival in the CTO artery territory. This distinction will facilitate the investigation of the effects of actively opening concurrent CTO lesion in MVD patients with necrotic myocardial tissue identified via CMR in the territory supplied by the CTO, aiming to provide reliable evidence for use in clinical practice.

CMR is an appropriate approach for the evaluation myocardial viability and cardiac function. The method is accurate, safe, and provides great spatial resolution as well as sensitivity.^[30]^ CMR has been used to assess myocardial viability throughout the previous decade. According to Cardona et al., CMR accurately detects myocardial viability in patients with reduced LVEF.^[17]^ We previously demonstrated that, using PET as gold standard, CMR has high consistency, sensitivity, and specificity for the detection of myocardial viability compared with PET in CTO patients.^[31]^ Therefore, in the SOS-moral trial, CMR will be used to evaluate both the amount of viable myocardial tissue and level of cardiac functioning.

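### The Conclusions claim that sorting patients by viability before randomisation avoids its effect, but only complete survival is screened out, and partly viable and non-viable patients stay pooled

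*Protocol article*

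**What the plan says.** The Introduction says that "the myocardium in the CTO territory can be divided into groups as follows: complete survival, partial survival, and non-viable myocardium", and it attributes conflicting earlier results partly to neglect of myocardial status or ischaemic burden. It adds that CMR will be used to assess viability, "which facilitates identification of patients who will benefit from complete revascularization procedures".

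On who is screened out, the Abstract says "Patients presenting with no necrosis of myocardial tissue in the territory of the CTO will be excluded" and the Discussion says "The present SOS-moral study excludes those patients with complete myocardial survival in the CTO artery territory". Section 2.3.1 words the entry criterion differently: a previous myocardial infarction, with no territory named, or CMR necrosis in the CTO territory. It sets no upper limit on necrosis.

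On allocation, section 2.1 has patients "categorized into two groups at a ratio of 1:1 according to a randomized digital table" and names no stratification factor. It does have viability assessed by CMR before the intervention. Section 2.8 describes two-sample comparisons between the arms, with no viability term.

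The Conclusions then state that "SOS-moral will sort myocardial viability before randomization to avoid the effect of viability of myocardial on cardiac function". The next sentence of the Conclusions limits the target to patients whose myocardium is not fully viable.

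**The concern.** The sentence in the Conclusions credits the design with a property it does not have. Removing one of three viability classes narrows the population but does not remove viability as a source of variation in the treatment effect among those enrolled. The article itself treats viability as a modifier: the Discussion reports, from an earlier CMR substudy, that recovery was clearest in impaired segments with infarction through less than half the wall.

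Interpretation is what is at stake. If the pooled LVEF comparison is null, a reader could not tell an absence of benefit from a benefit in partly viable territory diluted by non-viable territory. The authors raise much the same ambiguity about earlier trials. A reader who trusts the sentence would also believe that the question had been settled by design.

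**Working it through.** **1. The wording against the design.** There are two ways to read the sorting.

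- As stratification: 2.1 describes 1:1 allocation from a random number table and mentions no viability factor.
- As screening: the Abstract and Discussion remove complete survival only. With no upper limit on necrosis in 2.3.1, partial survival and non-viable territory both enter.

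On neither reading, as described, is the effect of viability avoided. Even the screen is not secured. The alternative in 2.3.1 admits a patient with an old infarct in another territory and a fully viable CTO territory, and the exclusion list in 2.3.2 contains nothing to stop this.

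**2. The plan's own sample size.** Inputs from 2.7: SD 9 points, boundary value 4 points, one-sided alpha 0.025, power 0.90, 10% loss.

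- Normal approximation: n per arm = 2 × 9² × (1.960 + 1.282)² / 4² = 106.4, so 107.
- t-test version: 107.36, so 108 per arm, or 216 in total. Then 216 / 0.90 = 240.

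The stated 216 and 240 are reproduced when 4 points is the difference to detect. Using 6.5 points gives 82 to 84 in total. Using 6.5 − 4 = 2.5 gives 546 to 548. (The figure of 226 in the same section matches none of these. That is a separate matter and is not used here.)

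**3. Dilution.** Let q be the share of non-viable patients. The documents give no value, so q is an assumption, as is zero gain in these patients. If the others gain e points, the pooled effect is (1 − q) × e. With 108 per arm, SE = 9 × √(2/108) = 1.225, and power = Φ((1 − q)e / 1.225 − 1.96).

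| q | Pooled effect, e = 4 | Power | Pooled effect, e = 6.5 | Power |
|---|---|---|---|---|
| 0 | 4.00 | 0.90 | 6.50 | >0.99 |
| 0.1 | 3.60 | 0.84 | 5.85 | 0.998 |
| 0.2 | 3.20 | 0.74 | 5.20 | 0.99 |
| 0.3 | 2.80 | 0.63 | 4.55 | 0.96 |
| 0.5 | 2.00 | 0.37 | 3.25 | 0.76 |

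**4. Treatment-by-viability interaction.** With N = 216, SE = 9 × √(4/(Nq) + 4/(N(1 − q))), tested two-sided at 0.05.

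| q | SE | Power, 4-point difference in effects | Power, 6.5-point difference |
|---|---|---|---|
| 0.1 | 4.08 | 0.16 | 0.36 |
| 0.2 | 3.06 | 0.26 | 0.56 |
| 0.3 | 2.67 | 0.32 | 0.68 |
| 0.5 | 2.45 | 0.37 | 0.76 |

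The trial is sized for one pooled comparison, not for this one.

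**The case against.** The strongest reply is that sorting means screening. The next sentence of the Conclusions says as much, and the average effect in patients with necrosis is a legitimate target that the Introduction names. This stands: the design answers a valid question, and the defect is the claim made for it. It does not rescue the words about avoiding viability's effect.

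A second reply is that a condensed article may leave stratification factors and subgroup analyses to the full protocol or the analysis plan, neither of which is shown. That also stands, so their absence is not counted here as an error. The misstatement does not depend on it.

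A reader might go further in three ways that the documents do not support.

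- **That the trial cannot identify who benefits.** Baseline CMR viability is recorded, so effects by class can be estimated. What can be said is that the article describes no such analysis and the sample is not sized for one.
- **That unstratified allocation biases the result.** Viability is balanced in expectation, and chance imbalance matters little. At an assumed 30% share, the 95% range for the CTO-PCI arm is ±1.96 × √(0.3 × 0.7/108) = ±0.086. If viability alters only the response to CTO-PCI, with gains of 4 and 0 points, that is about 0.35 points against an SE of 1.225.
- **That the non-viable share is 11.5 / (100 − 58.6) = 28%.** These Discussion figures describe regions or segments, not patients. An eligible patient can have many segments without enhancement.

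The substudy evidence also concerns regional function at four months in patients with STEMI. Carrying it over to global LVEF at 12 months is an assumption.

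**Conclusion.** The point holds as a misstatement about the design with a consequence for interpretation. As described, screening removes complete survival at most, the two remaining classes are pooled, and the effect of viability is not avoided. The pooling itself does not invalidate the comparison of arms. The exclusions that 2.8 makes after randomisation are a different question.

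The size of any dilution is unknown. It rests on an assumed non-viable share and an assumed zero gain in those patients. It is substantial if the gain in the others is near the 4 points that reproduce the sample size (power 0.63 at a 30% share). It is small if the gain is the 6.5 points cited in 2.7 (0.96 at the same share). The change is worth making, but it does not call for a redesign.

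**What to change.** 1. **Conclusions.** Replace the sentence with a statement that only patients with complete survival in the CTO territory are excluded, and that the trial estimates the average effect in a population of mixed viability.
2. **Section 2.8.** Pre-specify one treatment-by-baseline-viability analysis of the 12-month LVEF change, with the effect and its interval reported in each class. Define how segment readings give a patient's class before outcome data are examined. Label the analysis as imprecise: power is about 16% to 37% for a 4-point difference in effects.
3. **Section 2.1.** If enrolment has not started, add baseline CMR viability class as a stratification factor in the existing randomisation system. If a fuller document already holds items 2 or 3, a cross-reference is enough.
4. **Section 2.3.1.** Reconcile the infarction-or-necrosis criterion with the exclusion stated in the Abstract and Discussion, so that it is clear whether a fully viable CTO territory can enter.

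The rewording costs nothing, and the analysis uses CMR data that are already collected, so both remain possible after enrolment has begun. Stratification requires the viability class to be read before allocation. The class-specific estimates will be imprecise, so a null interaction should not be read as evidence that viability is irrelevant.
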